#### **8.3.2 Secondary Endpoint(s)**

The secondary endpoints in this study include

- ①. Effective endpoints:
  - i. RHR
  - ii. BPV
  - iii. Blood pressure: peripheral and central blood pressure
- ②. Safety endpoints: AEs recorded in this study
- ③. Compliance Analysis

### **8.4 Analysis Sets**

#### **8.4.1 PP and ITT Analysis**

The main analysis set will be defined as all subjects who receive at least one dose of any investigational medicinal product, i.e., the Intention-to-Treat (ITT) population. This population will be used for all efficacy evaluations. A secondary analysis set, the Per Protocol

(PP) set, will also be defined, which will exclude all subjects found to have a major protocol deviation\*.

\*Deviation from the protocol will be determined by medical check.

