### **5.3.4 Randomization:**

This study is a parallel, randomized, controlled study, Patient will be randomized by the predesigned randomization schedule using randomization envelope.

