### **5.3.5 Criteria for Subject Withdrawal**

Subjects are free to discontinue the trial at any time without giving their reasons.

A subject must be withdrawn in the event of any of the following:

1. Withdrawal of the subject's consent.
2. Occurrence of an exclusion criterion which is clinically relevant and affects the subject's safety, if discontinuation is considered necessary by the Investigator.
3. Intolerance to Concor® treatment.
4. Occurrence of unexpected adverse events that are unacceptable in nature, severity and/or duration, or the frequency of known unacceptable adverse events is higher than expected.

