## **7.1 Trial procedures and assessments**

### **7.1 Trial schedule and assessment contents**

The trial procedure and assessment contents are as follows:

1. Visit 1 -Week -1 (1 +3 day): this visit entails the following:

Before any procedures that are related to the trial is undertaken, informed consent of the patient should be obtained. Thereafter, basic information of the patient will be obtained and patients are screened for eligibility based on the inclusion and exclusion criteria.

- ①. Record birth date, gender, height, weight, waist circumstance, current medical condition and past medical history, including concomitant therapies.
- ②. Perform physical examinations, including vital signs (blood pressure, heart rate).
- ③. Blood tests: full blood count (white blood cells, neutrophils, red blood cells, hemoglobin and platelets), liver function (ALT, AST), renal function (Bun, Cr), fasting blood glucose and blood lipids (TC, TG, LDL-C and HDL-C).
- ④. 12-Lead ECG and echocardiography

- ⑤. Sepical tests: central blood pressure, BRS, BPV, HRV, Holter and 24 h-ABPM
2. Visit 2-Week 2 (14+3 days): this visit entails the following:
- ①. Perform physical examinations, including vital signs (blood pressure, heart rate), 12-Lead ECG.
  - ②. If the RHR is lower than 65 bpm, test BRS, BPV, HRV. Remain the treatment for an extended 2-week, then go for Last visit.
  - ③. Record AE and concomitant therapies.
3. Visit 3-Week 4 (28 +3 days): this visit entails the following:
- ①. Perform physical examinations, including vital signs (blood pressure, heart rate), 12-Lead ECG.
  - ②. If the RHR is lower than 65 bpm, test BRS, BPV, HRV. Remain the treatment for an extended 2-week, then go for Last visit.
  - ③. If the RHR is still higher than 65 bpm, adjust the dosage of bisoprolol or atenol according to blood pressure and heart rate. After 2 weeks, go for Visit 4.
  - ④. Record AE and concomitant therapies.
4. Visit 4-Week 6 (42+3 days): this visit entails the following:
- ①. Perform physical examinations, including vital signs (blood pressure, heart rate), 12-Lead ECG.
  - ②. If the RHR is lower than 65 bpm, test BRS, BPV, HRV. Remain the treatment for an extended 2-week, then go for Last visit.
  - ③. If the RHR is still higher than 65 bpm, directly go for Last visit.
  - ④. Record AE and concomitant therapies.
5. Last Visit- End of extended treatment:
- ①. Perform physical examinations, including vital signs (blood pressure, heart rate), 12-Lead ECG.

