### **8.2 Randomization**

Patient will be randomized in a 1:1 ratio.

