#### **8.4.3 Safety Analysis**

The set of subjects included in the safety analysis is those subjects who receive at least one dose of trial drug and who have follow-up safety data.

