### **8.5 Description of Statistical Analyses**

#### **8.5.1 General Considerations**

All statistical tests will be performed at the 0.05 significance level. 95% confidence intervals will be calculated whenever appropriate.

Only available data will be considered for analysis. Subjects who discontinue the study prematurely will be considered as missing data and will be dropped from the statistical analysis.

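### The main efficacy set is called ITT but requires a first dose, and section 8.5.1 then drops every premature discontinuer, so the main comparison is not intention-to-treat

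*Protocol*

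**What the plan says.** Protocol section 8.4.1 defines the main set: "The main analysis set will be defined as all subjects who receive at least one dose of any investigational medicinal product". It names this the ITT population and adds: "This population will be used for all efficacy evaluations". The per-protocol set in the same section is narrower still, because it removes major deviators.

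Section 8.5.1 limits the analysis to available data and states: "Subjects who discontinue the study prematurely will be considered as missing data and will be dropped from the statistical analysis".

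On allocation, section 5.3.4 says: "Patient will be randomized by the predesigned randomization schedule using randomization envelope". The first of the two sections numbered 8.2 says: "Patient will be randomized in a 1:1 ratio". The primary endpoint (8.3.1) is BRS and central blood pressure at the Last visit.

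The safety set (8.4.3) is "those subjects who receive at least one dose of trial drug and who have follow-up safety data". The first scheduled visit on treatment is introduced in section 7.1 as "Visit 2-Week 2 (14+3 days): this visit entails the following".

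**The concern.** An intention-to-treat comparison keeps each randomised patient in the assigned group, so that what happens after allocation cannot change who is compared. Here two later events do change it: taking a first dose (8.4.1) and staying to the end (8.5.1).

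A first-dose condition does little harm when the decision to start cannot depend on the arm. The protocol does not document that protection. Allocation is by envelope and no masking is described in the text available. Section 5.1 gives bisoprolol once daily and atenolol twice daily, whereas section 6.2 gives once daily for both; those sections must be reconciled, but the first would make the arms visibly different. The mandatory withdrawal list in section 5.3.5 includes "Intolerance to Concor® treatment", a brand name that in context means the bisoprolol product, and has no matching entry for atenolol. Read literally, early exits could arise by different rules in the two arms.

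What is at stake is the primary comparison: it would be reported as ITT while resting on dosed patients who completed.

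**Working it through.** **Who is counted, section by section**

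| Subject | 8.4.1 main set | After 8.5.1 |
|---|---|---|
| Randomised, never dosed | out | out |
| Dosed, leaves early | in | dropped |
| Dosed, reaches Last visit | in | analysed |

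The two sections also disagree on the middle row: 8.4.1 uses the whole dosed set for efficacy, and 8.5.1 removes part of it. Changing 8.4.1 alone would hardly alter who is analysed at the Last visit, because 8.5.1 would still remove anyone who left.

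**What early leavers can contribute.** Under section 7.1, BRS is measured at Visits 2 to 4 only if resting heart rate is below 65 bpm. Central pressure is measured only at Visit 1 and the Last visit. Retained interim data can therefore help for BRS in some leavers, but not for central pressure.

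**Size for efficacy.** The plan gives no figure to reproduce: 110 patients are stated without effect size, SD, power or dropout. Inputs:
- From the protocol: 110 patients at 1:1, so 110/2 = 55 per arm, and significance level 0.05. (Section 5.1 also prints 96 beside each arm, which does not match 110 and is a separate matter.)
- Assumed: two-sided test; a fraction f of one arm lost and none of the other; those lost would have had a Last visit mean k SD away from those retained in the same arm.

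Bias = f × k. Standard error = √(1/[55(1 − f)] + 1/55) in SD units. Type I error = Φ(−1.960 − bias/SE) + 1 − Φ(1.960 − bias/SE).

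Example, f = 0.10 and k = 1.0: bias = 0.10; SE = √(1/49.5 + 1/55) = 0.196; ratio 0.510; type I error = 0.0067 + 0.0736 = 8.0%.

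| Lost from one arm | Bias, k = 0.5 to 1.0 | Type I error |
|---|---|---|
| 5% (about 3 patients) | 0.025 to 0.05 SD | 5.2% to 5.8% |
| 10% (5 to 6) | 0.05 to 0.10 SD | 5.8% to 8.0% |
| 15% (about 8) | 0.075 to 0.15 SD | 6.6% to 11.7% |

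**Safety set.** Assume that 12 of 55 patients on one drug have an AE and 3 of those 12 leave before Visit 2.
- If the site learns of the three events, those patients plausibly have follow-up safety data and are already counted: 12/55 = 21.8%.
- If the events are never learned of, the current set gives (12 − 3)/(55 − 3) = 9/52 = 17.3%, and a set of all dosed subjects gives 9/55 = 16.4%.

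So removing the follow-up condition does not restore 21.8%. Where events are not ascertained, it lowers the rate further.

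**The case against.** The best defence is that a dosed-only set is common, that a never-dosed patient has no Last visit value and so adds nothing to the primary comparison under either definition, and that the likely bias is small. Much of this stands. Redefining the set without touching 8.5.1 would be mostly cosmetic, and 5% loss in one arm moves the type I error only to between 5.2% and 5.8%. But the defence leaves a set under the wrong name and a rule that discards dosed leavers. Nor can it be met by pointing to a statistical analysis plan, since the protocol itself states both rules.

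Three stronger readings are tempting, and the documents do not support them.

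- A reader might infer that the safety set makes the drugs look better tolerated than they are. The arithmetic above does not show this: the gap to 21.8% comes from unascertained events, not from the definition. Section 7.4.1.2 requires all AEs during the study to be recorded, and 7.4.1.3 requires SAEs associated with study medication to be reported within 24 hours, so Visit 2 is not the only route.
- A reader might infer from the phrase about any investigational product that a patient given the other drug has no arm. That phrase settles who enters the set, not the arm in which they are analysed, which is commonly left to the statistical analysis plan.
- A reader might infer that these losses go unrecorded. Section 10.2 requires the date of and reason for early withdrawal in the subject file. What is missing is their place in the analysis.

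**Conclusion.** The point holds for efficacy. Sections 8.4.1 and 8.5.1 together produce a comparison of dosed patients who did not discontinue, labelled ITT, in a trial where nothing documented stops losses from depending on the assigned drug. The sections also contradict each other on dosed early leavers.

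The size cannot be fixed, because no refusal or dropout rate is given. Under the assumptions shown it runs from negligible with few losses to a type I error of about 8% with 10% lost from one arm and a 1 SD difference. If losses are balanced and unrelated to outcome, there is no bias of this kind.

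The safety set is a minor matter of transparency.

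The conclusion takes the trial as randomised, as in sections 5.1, 5.3.4 and the first 8.2. The second section numbered 8.2 says that no randomisation is needed and has to be reconciled separately. Absence of masking is judged from the text available; the study flow figure is not shown.

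**What to change.** 1. **Section 8.4.1.** Define the ITT set as all randomised subjects, analysed in the arm assigned by the randomisation schedule. If a dosed-only set is kept, call it a treated (modified ITT) set and report by arm how many were randomised but not dosed.
2. **Section 8.5.1.** Delete the sentence that drops premature discontinuers. Keep all their available post-baseline data in the main analysis, and add a sensitivity analysis for missing Last visit values. For central pressure, which has no interim measurement, that analysis carries most of the weight.
3. **Section 8.4.3 (minor).** Define the safety set as all dosed subjects by drug taken, and report by arm the number of exposed subjects without follow-up safety data. Do not present this as correcting the AE rate.

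Items 1 and 2 need to be made together. The cost is a few sentences of protocol text, a few subjects without outcome data in the denominators, and some added missing-data work. No further patients or procedures are needed.

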#### **8.4.2 Subgroup Analysis**

Subgroup analysis will be conducted within the subgroups defined according to drug dosage.

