**To compare the safety and compliance of bisoprolol and atenolol treatment after RHR<65bpm**

### **4.1 Primary objective**

To compare the efficacy in SNS activity and central blood pressure(CAP) of bisoprolol and atenolol in essential hypertensive patients with RHR>70bpm

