### **4.2 Secondary objective**

1. To compare the effect in other SNS indication of bisoprolol and atenolol in EH patients with RHR>70bpm
2. To compare the efficiency of bisoprolol and atenolol to attaining RHR<65bpm]
3. To compare the efficiency of bisoprolol and atenolol on peripheral blood pressure

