## 5. Study Design

### 5.1 Study Design

It is a single-centers, randomized study in China, and planned to enroll 110 essential hypertension patients from 1 sites, who will be assigned to two groups randomly. All the inclusive patients will be consistent with the diagnosis of essential hypertension, and have a resting heart rate(RHR)  $\geq 70$  beats per minutes(bpm).

The inclusive patients will be assigned to two groups as follow (ratio 1:1)

Arm A: bisoprolol, 5-10mg/day for a targeting heart rate of less than 65 bpm(96)

Arm B: atenolol, 50-100mg/day for a targeting heart rate of less than 65 bpm (96)

The patient will receive bisoprolol 5mg Qd.(or atenolol 25mg Bid) for 2 weeks. If his/her heart rate<65bpm, this initial dose will be prolonged for another 2 weeks before the observation is over.

If the heart rate>65bpm, the patient will receive bisoprolol 7.5mg Qd.( or atenolol 37.5mg Bid) for 2 weeks. Then if his/her heart rate<65bpm, this increased dose will be prolonged for another 2 weeks before the observation is over.

If the heart rate>65bpm, the patient will receive bisoprolol 10mg Qd.( or atenolol 50mg Bid) for 2 weeks. Then if his/her heart rate<65bpm, this increased dose will be prolonged for another 2 weeks before the observation is over. If the heart rate>65bpm, the observation is over directly.

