### **6.2 Dosage**

Initial period (2 weeks) : Bisoprolol 5mg qd or Atenolol 50mg qd

First dosage adjustment period (2 weeks) : Bisoprolol 7.5mg qd or Atenolol 75mg qd

Second dosage adjustment period (2 weeks) : Bisoprolol 7.5mg qd or Atenolol 75mg qd

Extended treatment period (2 weeks): When patient's heart rate is lower than 65 bpm, keep the dosage for 2 more weeks.

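### The one stated subgroup analysis splits patients by a dose set after randomisation by heart-rate response, so a between-drug comparison inside those strata can be biased; the safety/compliance objective also conflicts with the safety analysis set

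*Protocol*

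**What the plan says.** Section 8.4.2 is a single sentence: "Subgroup analysis will be conducted within the subgroups defined according to drug dosage". It names no endpoint and no test, and does not say whether the drugs are compared within each stratum. It is the only subgroup analysis in the protocol.

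Section 5.1 sets the dose by response. At two weeks: "If the heart rate>65bpm, the patient will receive bisoprolol 7.5mg Qd.( or atenolol 37.5mg Bid) for 2 weeks". At the next step: "If the heart rate>65bpm, the patient will receive bisoprolol 10mg Qd.( or atenolol 50mg Bid) for 2 weeks". A patient below 65 bpm stays on the current dose for two more weeks and then finishes. Section 7.1 repeats this scheme by visit and, at Visit 3, lets blood pressure as well as heart rate guide the adjustment. Section 6.2 describes the last step differently: "Second dosage adjustment period (2 weeks) : Bisoprolol 7.5mg qd or Atenolol 75mg qd".

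Reaching the heart-rate target is itself an outcome compared between the drugs (section 4.2): "To compare the efficiency of bisoprolol and atenolol to attaining RHR<65bpm".

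The Synopsis, and section 4 just above 4.1, carry a further objective: "To compare the safety and compliance of bisoprolol and atenolol treatment after RHR<65bpm". The numbered list in 4.2 does not repeat it. Section 8.3.2 takes as safety endpoint the adverse events recorded in the study, with no heart-rate condition. Section 8.4.3 has none either: "The set of subjects included in the safety analysis is those subjects who receive at least one dose of trial drug and who have follow-up" data on safety. Section 8.4.1 uses all dosed subjects for the efficacy evaluations.

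**The concern.** A subgroup supports a randomised comparison when membership is fixed before treatment starts. Here the drug itself helps to decide it. If one drug slows the heart more, its lowest-dose group takes in patients who would have been stepped up on the other drug, and its highest-dose group keeps only the most resistant. At every dose the arms then contain different kinds of patient.

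The protocol gives reason to take both conditions for bias seriously. It treats attainment of the target as a possible difference between the drugs. Section 7.2.6 defines BRS from pulse interval, which is the reciprocal of heart rate, and corrects the augmentation index because it depends on heart rate.

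At stake is a false claim that one drug does better at a given dose. The distortion runs the same way in all strata, so it could look like a consistent effect even where the full randomised comparison shows none.

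The objective on safety and compliance raises a related problem. Read literally, it starts the comparison only once the target is reached. That leaves out titration and patients who never reach the target, whereas the safety section includes both.

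**Working it through.** **Plan's own figure.** The protocol gives no number for this point. Its total of 110 (section 8.1) comes with no effect size, SD or power and cannot be reproduced, but the argument does not depend on it. Cell sizes below use 110/2 = 55 per arm, although section 5.1 also prints 96 against each arm. The study is taken as randomised 1:1 (sections 5.1, 5.3.4 and the first paragraph numbered 8.2).

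**Rule from the documents.** Step up while on-treatment heart rate exceeds 65 bpm, with three dose levels as in section 5.1.

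**Assumptions, not in the documents.** The outcome is in SD units and the true drug effect on it is zero. One drug lowers heart rate by d bpm more. The outcome has correlation ρ with the patient factor U that drives heart rate on treatment. Two sets of further inputs were simulated, each with about 2,000,000 patients per arm:

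- Set A: baseline heart rate about 78 (SD 5, above 70); first-step fall 10 bpm in one arm and 10 + d in the other (SD 6); a further 4 bpm fall at the second step.
- Set B: heart rate on the starting dose 67 in one arm and 67 − d in the other (between-patient SD 7, visit error SD 2); a further 3 bpm fall per step.

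**Results (absolute spurious difference, SD; ρ = 0.3 to 0.5)**

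| Set | d (bpm) | Lowest dose | Middle | Highest | All patients |
|---|---|---|---|---|---|
| A | 2 | 0.05–0.08 | 0.06–0.11 | 0.04–0.07 | 0.00 |
| A | 4 | 0.09–0.15 | 0.12–0.21 | 0.09–0.14 | 0.00 |
| A | 6 | 0.13–0.21 | 0.18–0.30 | 0.13–0.22 | 0.00 |
| B | 3 | 0.08–0.13 | 0.12–0.20 | 0.09–0.14 | 0.00 |
| B | 5 | 0.12–0.21 | 0.20–0.33 | 0.15–0.25 | 0.00 |

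With d = 0 or ρ = 0, every stratum is within simulation noise of zero (at most 0.005 SD).

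**Hand check, Set B, lowest dose.** Total SD = √(7² + 2²) = √53 = 7.28. With c = (65 − 67 + d)/7.28, the mean of U among those staying on the first dose is −(7/7.28) × φ(c)/Φ(c).

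- d = 0: c = −0.275, φ = 0.384, Φ = 0.392, mean = −0.943
- d = 5: c = 0.412, φ = 0.366, Φ = 0.660, mean = −0.534
- Difference = 0.409; × 0.3 = 0.123 and × 0.5 = 0.204, agreeing with the simulation.

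**Cell sizes and false positives.** In Set A with d = 4, the cells (faster-lowering drug against the other) are about 29 vs 18, 11 vs 11 and 15 vs 26. The standard errors √(1/n₁ + 1/n₂) are 0.30, 0.43 and 0.32 SD. With an assumed 20 per arm, SE = √(2/20) = 0.316. For bias b, the two-sided 5% test then rejects with probability 1 − Φ(1.96 − b/SE) + Φ(−1.96 − b/SE):

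- b = 0.10: 6%
- b = 0.20: 10%
- b = 0.25: 12%

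**Restriction to patients who reach the target.** In Set B, comparing only these patients gives 0.05 to 0.13 SD for d = 3 to 5 and ρ = 0.3 to 0.5.

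**Dose levels.** Section 5.1 gives three bisoprolol levels: 5, 7.5 and 10 mg. Section 6.2 gives 5, 7.5 and again 7.5 mg, which is two. The number of strata therefore depends on which section is read.

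**The case against.** Section 8.4.2 does not prescribe a test of one drug against the other within a dose; descriptive or within-arm summaries by dose would also fit, and a statistical analysis plan could say so. This stands in part: the between-drug reading is an inference. It is the natural one, because the objectives are framed as comparisons of the drugs, section 8.5.1 sets 0.05 for all tests, and nothing marks these subgroups as descriptive.

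A reader might infer that the subgroup results are certain to be biased. The documents do not support that. Both arms are titrated towards the same target, and equal heart-rate lowering, which gives no bias, is possible. Under the assumptions here the bias is also mostly below one standard error of a stratum comparison. This stands.

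A reader might also infer that safety is compared only in patients who reach the target. The operative text says otherwise. Section 7.4.1.2 records all adverse events, section 7.1 records them at the titration visits, and sections 8.3.2 and 8.4.3 set no heart-rate condition. For adverse events the defect is an objective at odds with its analysis set. Only compliance is left with no other stated scope, since section 8.3.2 merely names the analysis.

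Nor does the objective's wording cause the loss of patients who withdraw. That comes from section 8.5.1, which drops early discontinuations from the analysis, and rewording the objective would not change it.

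**Conclusion.** The point holds in a conditional form. The only subgroup analysis that the protocol states is defined by response after randomisation, so between-drug comparisons within dosage strata can be biased. Two conditions are needed: the drugs must differ in heart-rate lowering, and that response must be related to BRS or central pressure.

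The size, roughly 0.04 to 0.3 SD per stratum, is illustrative and rests wholly on the assumed inputs. The mechanism is firm; the magnitude is not. The main efficacy comparison in all dosed subjects (section 8.4.1) is not conditioned on dose, so this is a correction to a subsidiary analysis and no threat to the primary one.

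The safety and compliance objective contradicts sections 8.3.2 and 8.4.3 and needs aligning. The disagreement between sections 5.1 and 6.2 leaves the dosage strata without a consistent definition.

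**What to change.** 1. In section 8.4.2, report final dose, and outcomes by dose, descriptively for each arm, with no between-drug test inside dose strata.
2. Base any between-drug subgroup comparison on variables measured before treatment and already collected at Visit 1, for example baseline resting heart rate or baseline central pressure, using a treatment-by-subgroup interaction.
3. Remove the heart-rate condition from the safety and compliance objective in the Synopsis and section 4. State that adverse events and compliance are compared from first dose in all treated subjects, in line with sections 8.3.2 and 8.4.3.
4. Reconcile sections 5.1 and 6.2 on the second-adjustment dose, so that a table by dose has defined rows.

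The cost is wording only, with no new data or visits. Dose-specific claims of one drug over the other are given up. With roughly 10 to 30 patients per cell, such claims would have been imprecise anyway.
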